## Methods

### Study Design and Subject Selection

#### Study Type

This is a retrospective and prospective, observational study. The Investigators acknowledge that a possible limitation of measuring and comparing the treatment effect of the team-based approach with historical controls not exposed to team intervention may present selection bias due to the change in treatment paradigm, potential loss of blinding, lack of true point estimates, and increased risk of type I error.

#### Setting or Location

Outpatient or inpatient chart review utilizing EPIC, the electronic medical record utilized by the Inova Health System (HIS) for patients admitted to Inova Fairfax Medical Campus. EPIC review will occur at the Center for Thrombosis Research and Drug Development Center: [name], Inova Heart and Vascular Institute 3rd Floor, [name].

#### Duration of Study

Chart review in EPIC will occur over a one-year period.

#### Number of Subjects

Our goal is to include approximately 200 patients before and 200 patients after initiation of Shock team. The study group will consist of a retrospective review of all patients receiving Shock Team intervention after diagnosis with acute decompensated heart failure cardiogenic shock, or acute myocardial infarction cardiogenic shock, from January 1, 2017 until Institutional Review Board (IRB) filing of protocol. A second group will consist of current patients receiving shock team intervention.

#### Study Population

##### Gender of Subjects

There are no gender-based enrollment restrictions. Subjects will include a distribution based on the demographics of the Northern Virginia population.

##### Age of Subjects

Anyone 18 years or older who underwent CS team intervention for acute decompensated heart failure cardiogenic shock, acute myocardial infarction cardiogenic shock will be included.

##### Racial and Ethnic Origin

There are no race-based enrollment restrictions. Subjects will include a distribution based on the demographics of the Northern Virginia population.

##### Vulnerable Populations

No vulnerable populations will be enrolled in this study.

#### Recruitment

Preliminary chart review in EPIC will be performed on all patients in our practice and those who have a previously undergone Cardiogenic Shock team intervention for acute decompensated heart failure cardiogenic shock, or acute myocardial infarction cardiogenic shock. No recruitment process will be necessary to obtain information.

#### Inclusion Criteria

Patients at the IHVI with documented Cardiogenic Shock team intervention for acute decompensated heart failure cardiogenic shock, or acute myocardial infarction cardiogenic shock.

Specific criteria for the diagnosis of cardiogenic shock is defined by hemodynamic parameters—systolic blood pressure <90 mm Hg, cardiac index <1.8 L/min/m^2^ without pharmacologic support (or >2.2 L/min/m^2^ with support), left ventricular end-diastolic pressure >18 mm Hg or right ventricular end-diastolic pressure >10-15 mm Hg or pulmonary capillary wedge pressure >15 mm Hg—and clinical signs and symptoms of hypoperfusion, such as cool extremities, decreased urine output, and altered mental status.

Enrollment criteria are specific to patients treated at the IHVI for documented cardiogenic shock with activation of the IHVI Cardiogenic Shock team. Cardiogenic shock will have preceded acute decompensated heart failure or acute myocardial infarction etiologies. Patients will include those transferred from offsite hospitals as well as inpatients at the IHVI.

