**Methods:**

This is an observational, retrospective, single center study. Retrospective and prospective data will be collected in patients treated at the Inova Heart and Vascular Institute with documented cardiogenic shock as a result of acute decompensated heart failure or acute myocardial infarction. This registry will include data from patients prior to and after the initiation of the multidisciplinary Cardiogenic Shock team on January 1, 2017. Clinical outcomes associated with early multidisciplinary team intervention will be analyzed. In the study group, all patients evaluated for documented cardiogenic shock (acute decompensated heart failure cardiogenic shock, acute myocardial infarction cardiogenic shock) treated at the Inova Heart and Vascular Institute by the Cardiogenic Shock team will be included. An additional historical Inova Heart and Vascular Institute control group will be analyzed as a comparator. Means with standard deviations will be reported for outcomes. For categorical variables, frequencies and percentages will be presented. For continuous variables, the number of subjects, mean, standard deviation, minimum, 25th percentile, median, 75th percentile and maximum will be reported. Reported differences will include standard errors and 95% CI.

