The implementation and utilization of a designated CS at the IHVI is an effective strategy to mitigate the consequences of cardiogenic shock. The IHVI CS team, founded in 2017, is mobilized for and directed to five goals: (1) the rapid identification of shock through early activation of the CS team and rapid collaborative decision making, (2) early right heart catheterization to facilitate invasive hemodynamic therapy tailored to the patients’ unique presentation, (3) the accelerated initiation of mechanical circulatory support, (4) minimization of vasopressor and inotropic support, and (5) meaningful recovery and survival of the patient [13]. Bi-weekly action and outcomes review are employed to track efficient methodology with the intention of eradicating significant preventable morbidity and death from CS [13]. Utilizing the best and most recent evidence and best practices, a comprehensive care pathway was developed. A six-month training process was focused on individual and team management of the aforementioned five goals, training and rehearsals were implemented to ensure the seamless execution of the adopted algorithms [13]. Prior to implementation of the Cardiogenic Shock team at the IHVI, 30-day survival was approximately 47%, assuming an alpha level of 0.5, two sided. We expect the implementation of an IHVI Shock algorithm to increase 30-day survival by 15%. Thus, 200 subjects in each group provide at least 80% power to detect a statistically significant increase in 30-day survival from 47%.

We propose to study the outcomes associated with CS patients who have been managed by the CS team at the IHVI in order to ascertain the effects on outcome and survival rate. Positive effects in outcomes and survival will indicate a positive correlation between meaningful survival and management by a multidisciplinary shock team. The database compiled from these outcomes will also serve as a clinical archive of distinctive patient characteristics and outcomes to support future evaluation and translational research. The benefit of CS management to patients is a decrease in disability and mortality post CS episode.

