### Research Database Participation Eligibility

#### Participant Eligibility Criteria

Any patient with cardiogenic shock, whether inpatient or transferred from another facility, treated at the Inova Heart and Vascular Institute. This includes adults with and without decision making capacity over the age of 18 years old.

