## Results

Preliminary data analysis for the year 2017 has been completed. Compared to a baseline 2016 survival rate of 47.0%, from 2017 to 2018, CS survival rates were increased to 57.9% (81/140) and 81.3% (26/32), respectively (*P*=.01 for both). Survival in acute MI with CS increased from 52.6% (30/57) to 75.0% (12/16) and in acute decompensated HF from 61.4% (51/83) to 87.5% (14/16). For 2017, CS threshold markers at 12 hours (lactate<3.0 mg/dL, CPO>.6 W, PAPi>1.0) overall survival was 80% (72/90), 93.6% (73/78) and 74% (71/96), respectively. For 2018, CS threshold markers at 12 hours (lactate<3.0 mg/dL, CPO>.6 W, PAPi>1.0), overall survival was 92.3% (24/36), 92% (23/25) and 85.2% (23/27), respectively. Use of RHC was associated with 14% greater survival. Decreases of 5 and 10 hours in the time to implement MCS were associated with increased survival 53.6% and 135.8%, respectively. Age was associated with survival; patient’s ≥75 years old had higher risk of death (odds ratio 3.43, 95% CI 1.20-9.78).

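### The shock definition relies on catheter measurements that the team intervention itself promotes, and no common case definition is fixed for both eras, so case verification may differ before and after the team

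*Protocol article*

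**What the plan says.** All references are to the protocol article.

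- **Inclusion Criteria.** "Specific criteria for the diagnosis of cardiogenic shock is defined by hemodynamic parameters". The list has a systolic pressure, a cardiac index and one filling pressure ("left ventricular end-diastolic pressure >18 mm Hg or right ventricular end-diastolic pressure >10-15 mm Hg or pulmonary capillary wedge pressure >15 mm Hg"), joined to clinical signs of hypoperfusion. The same section adds: "Enrollment criteria are specific to patients treated at the IHVI for documented cardiogenic shock with activation of the IHVI Cardiogenic Shock team".
- **Participant Eligibility Criteria.** A wider rule: "Any patient with cardiogenic shock, whether inpatient or transferred from another facility, treated at the Inova Heart and Vascular Institute". It has no hemodynamic criterion and no team activation.
- **Background and Significance.** The second of the team's five goals is "early right heart catheterization to facilitate invasive hemodynamic therapy tailored to the patients’ unique presentation".
- **Abstract, Methods.** "An additional historical Inova Heart and Vascular Institute control group will be analyzed as a comparator". No section gives this group its own case definition.
- **Results.** "Use of RHC was associated with 14% greater survival". Survival is 47.0% in 2016, 57.9% (81/140) in 2017 and 81.3% (26/32) in 2018.

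**The concern.** The main comparison is survival before and after the team began. It is interpretable only if a shock case means the same thing in both periods.

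The filling pressures listed in Inclusion Criteria are catheter measurements, and the cardiac index normally comes from catheterization too. The intervention under study promotes one of the procedures that supply these values. An abstractor who applies Inclusion Criteria literally drops patients without invasive data. One who applies Participant Eligibility Criteria keeps them. The two cohorts differ in exactly the patients whom the Results report as surviving less often.

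If early catheterization was less common before it became a program goal, the split also falls differently by era. Part of the survival difference could then reflect how shock was verified. Removing the team-activation requirement, which no 2015-2016 patient can meet, would not cure this.

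**Working it through.** **Step 1. Can the written definition be met without a catheter?** No. Each of the three alternative filling pressures is a catheter measurement. LVEDP, however, can come from a left-sided study, so the definition needs invasive data but not necessarily RHC. RHC use is therefore only a proxy for meeting the definition.

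**Step 2. Were patients without RHC analysed?** Yes, by implication: a comparison by RHC use needs patients on both sides. Either the definition was not enforced for them, or they qualified through data that Inclusion Criteria do not describe. Their number is not given.

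**Step 3. The plan's own figures.** 81/140 = 57.9%, as printed in Results. The 2016-to-2017 difference is 57.9 - 47.0 = 10.9 points. (The Abstract prints other fractions beside the same percentages; the Results fractions reproduce them.)

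**Step 4. How many 2017 patients could lack RHC?** Results give 96 patients with PAPi>1.0 at 12 hours in 2017. Assume that PAPi requires RHC. The RHC share is then p ≥ 96/140 = 0.69, and at most 140 - 96 = 44 patients lacked it. For 2018, p ≥ 27/32 = 0.84, and at most 5 lacked it.

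**Step 5. How far would restriction to RHC patients move survival?** Write S = p·S_RHC + (1-p)·S_noRHC, and assume that the 14% applies to the year in question.

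- *14% as percentage points:* S_RHC - S = 14 × (1-p). For 2017 this is at most 14 × 44/140 = 4.4 points, and 4.4/10.9 = 40% of the reported difference. For 2018 it is at most 14 × 5/32 = 2.2 points.
- *14% as relative:* S_noRHC = 57.9/(1 + 0.14 × 0.686) = 52.8%, and S_RHC = 1.14 × 52.8 = 60.2%. The shift is 60.2 - 57.9 = 2.3 points, or 21% of the difference.

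**Step 6. Direction.** Let p_T and p_C be the RHC shares in 2017 and in the controls. On the points reading, assumed to hold in both eras:

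- Restricting 2017 only widens the difference by 14 × (1-p_T), at most 4.4 points.
- Restricting both eras changes it by 14 × (p_C - p_T). With p_T = 0.69 and assumed p_C of 0.9, 0.6 and 0.3, the control shift is 1.4, 5.6 and 9.8 points. The difference becomes 10.9 + 4.4 - 1.4 = 13.9, 10.9 + 4.4 - 5.6 = 9.7, and 10.9 + 4.4 - 9.8 = 5.5 points.

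The documents give no value for p_C. If RHC was rarer before 2017, strict use in both eras shrinks the apparent benefit. Strict use in the team era alone inflates it.

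**The case against.** Five points can fairly be made on the other side.

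- **RHC was not an entry gate.** A reader might infer that patients had to survive to catheterization to enter. The documents do not support that: the RHC comparison implies that patients without it were analysed, LVEDP needs no right heart catheter, and no section reports leaving out early deaths. This stands. Selective loss of early deaths is a risk if the definition is enforced, not a documented event.
- **The reported gain is not explained this way.** A reader might infer that verification accounts for nearly all of the 10.9 points. With 2017 RHC coverage at 0.69 or more, it cannot exceed about 4.4 points through 2017. If the 57.9% already includes patients without RHC, as Results suggest, restriction did not produce it at all. This also stands.
- **The scale of the 14% is unclear.** The next sentence of Results gives increases of 53.6% and 135.8%, and the latter cannot be percentage points. Hence both readings are shown above.
- **Era dependence through RHC is an inference.** RHC use in 2015-2016 is not reported. The explicit era-dependent criterion is team activation, which is a separate defect.
- **Partly disclosed or delegated.** Study Type concedes selection bias against historical controls, and Data Management mentions a data dictionary and trained abstractors. The concession is general and offers no remedy. A data dictionary could settle unclear charts, but the article itself prints two conflicting entry rules, and that is not detail left to another document.

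**Conclusion.** The point holds as a risk of differential case verification in the primary before/after comparison. The written definition rests on invasive measurements that the intervention promotes, the two eligibility sections conflict, and no common definition is fixed for the controls.

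The direction is uncertain. For 2017, the most that restriction to RHC patients could move survival is about 4.4 points (about 2.3 if 14% is relative), against 10.9 reported. These are sensitivity bounds, not estimates of bias in the published figures. They assume that PAPi requires RHC, that the 14% contrast applies to 2017, and that RHC stands in for invasive confirmation. The documents do not support reading this as a catheterization survival requirement or as the explanation of the reported gain. It is a modest weakness that is cheap to correct.

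**What to change.** - Reconcile Inclusion Criteria and Participant Eligibility Criteria into one case definition that can be applied from the chart in the same way to 2015-2016 and 2017-2018.
- State how patients without invasive data, and patients who die before catheterization, are classified.
- Record for each patient whether the invasive criteria were confirmed, and report the number confirmed in each era.
- Repeat the survival comparison in the confirmed subset as a sensitivity analysis.

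The cost is protocol wording, one extra chart field and a primary population that is less hemodynamically specific; the confirmed-subset analysis addresses the last. Which hemodynamic thresholds are right is left to the investigators.

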CS, also known as “pump failure” is precipitated by a profound reduction in cardiac output which results in tissue hypoperfusion secondary to a deficit of circulating blood, this lack of perfusion results in increasingly poor clinical outcomes [2,3,4]. Also defined as complete circulatory collapse, CS is characterized by shock occurring after a primary cardiac pathology in which cardiac output has been compromised. It involves refractory hypotension and tissue hypoperfusion secondary to heart failure after correction of preload and the culprit precipitating arrhythmia [2]. CS is representative of a diverse and complex clinical presentation which is the challenge of identification and management of this calamity. The onset of CS can be acute or progressive, as the ischemia representative of CS may develop from an acute, large, primary MI or can occur as a delayed extension of an original MI [2]. CS can occur acutely in patients with no prior history of cardiac disease, or progressively in patients with chronic heart failure [4]. The most common etiology of acute CS is the incidence of an acute coronary syndrome (ACS), specifically ST-segment elevation myocardial infarction (STEMI) or non-ST-segment elevation myocardial infarction (NSTEMI) which collectively has been reported to account for nearly 80% of cardiogenic shock cases [4]. Patients that develop CS post NSTEMI tend to develop dormant CS and are older with more complex cardiac comorbidities [2]. CS is the strongest predictor of mortality post MI. This is thought to result from both ischemic and mechanical complications. Mechanical complications of MI that contribute to CS include: acute mitral regurgitation secondary to rupture of the papillary muscle, rupture of the ventricular septal wall, or tearing of the ventricular wall [4]. CS can also arise from non-ACS causes such as cardiac abnormality (primary, valvular, electrical, or pericardial), decompensated valvular disease, acute myocarditis, hypertrophic cardiomyopathy with aortic obstruction, cardiac tamponade, arrhythmia, traumatic injury to the chest (myocardium), post cardiotomy secondary to coronary artery bypass graft surgery, and progression of congenital lesions [4].

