
A review of relevant literature identifies the benefit and recommends the implementation of a multidisciplinary shock team to improve outcomes in patients in danger of imminent circulatory collapse. Proposed recommendations are wide in scope yet highly specialized with respect to the requirements of this patient population. CS associated with acute MI or acute decompensated heart failure should be closely monitored for progression to decompensation and end organ failure. CS should be suspected and investigated post cardiac arrest due to the significant association between the two conditions by a multidisciplinary shock team [7]. Recommended personnel include a multidisciplinary oversight panel as well as experienced medical teams at a given site [7]. Medical, interventional cardiology, anesthesia, thoracic and vascular surgery, intensive care, and radiology [7] must be available to manage CS in a timely manner. The two strongest priorities in CS are hemodynamic stabilization and the rapid reversal of the low output state to maintain end organ perfusion and rapid coronary reperfusion, although not necessarily in that order, are optimally managed by a CS team [8,9]. Rehospitalization and death are most prevalent in the early discharge period [10]. These readmissions are frequently associated with volume overload as opposed to late readmissions which are associated with the natural trajectory of the syndrome for example cardiac remodeling [10]. This identifies the early discharge period as one where the patient is particularly vulnerable and the careful coordination of the multidisciplinary team as well as the transitional team are implemented to ensure that the care is patient-centered, as well as proactive in protection against recurrence of CS [10]. Activation of a coordinated cardiogenic shock team and early outcome specific therapy in a timely and synchronized manner ensures proper allocation of resources and is associated with increased survival in cardiogenic shock [11]^.^ Successful device selection to support heart rate (HR) in underlying CS etiologies is enhanced by a multidisciplinary team approach including; heart failure specialists, interventional cardiologists, and cardiothoracic surgeons, with patients’ preferences accommodated in a timely manner [12].

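### The printed diagnostic criteria contradict the protocol's own account of cardiogenic shock: on support, a cardiac index above 2.2 qualifies and a lower one does not, and shock is placed before its causes

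*Protocol article*

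**What the plan says.** The Inclusion Criteria give a hemodynamic and clinical definition of cardiogenic shock. Its parts are:

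- a blood pressure criterion, "systolic blood pressure <90 mm Hg";
- an index criterion, "cardiac index <1.8 L/min/m^2^ without pharmacologic support (or >2.2 L/min/m^2^ with support";
- a filling-pressure criterion with three alternatives joined by 'or': left ventricular end-diastolic pressure above 18 mm Hg, "right ventricular end-diastolic pressure >10-15 mm Hg", or wedge pressure above 15 mm Hg;
- clinical signs of hypoperfusion.

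The same section then states the order of events: "Cardiogenic shock will have preceded acute decompensated heart failure or acute myocardial infarction etiologies".

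Elsewhere the article describes the condition differently. Background and Significance says that it is "precipitated by a profound reduction in cardiac output which results in tissue hypoperfusion", characterizes it as "shock occurring after a primary cardiac pathology in which cardiac output has been compromised", and names among the treatment priorities "the rapid reversal of the low output state to maintain end organ perfusion". The Methods paragraph of the Abstract describes the study patients as having "documented cardiogenic shock as a result of acute decompensated heart failure or acute myocardial infarction".

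**The concern.** An eligibility definition should pick out the condition that the study is about. Here the supported limb of the index criterion points the opposite way from the unsupported limb and from the low-output description in the Introduction. The sentence on sequence puts the consequence before the cause.

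The main result is a before/after comparison of survival, which needs the same disease definition in both periods. The other entry condition in the Inclusion Criteria is intervention by, or activation of, the shock team. The team began on January 1, 2017, and the Hypothesis names 2015 and 2016 as the comparison years, so no control can meet that condition. For the controls, the diagnostic definition is the only part of the Inclusion Criteria left to apply, and it is the part that is misprinted or mis-stated.

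**Working it through.** There is no figure in the plan to reproduce. The check is a literal evaluation of the printed rule and a comparison of passages.

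**1. Index criterion.** Inputs, from the Inclusion Criteria: without support, qualify if index < 1.8; with support, qualify if index > 2.2 (L/min/m²).

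| Index | Without support | With support |
|---|---|---|
| 1.5 | qualifies | rejected |
| 1.79 | qualifies | rejected |
| 1.8 | rejected | rejected |
| 2.0 | rejected | rejected |
| 2.2 | rejected | rejected |
| 2.21 | rejected | qualifies |
| 3.0 | rejected | qualifies |

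An index of 1.5 meets the criterion without support and fails it with support. Every supported patient at or below 2.2 is rejected, including those with the lowest output. Background and Significance describes a profound fall in output and a low-output state, and no passage explains why the direction should change under support.

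**2. What else an admitted patient must meet.** I read the listed parameters as jointly required, with 'or' applying only within the filling pressures. A supported patient above 2.2 must then also have a systolic pressure below 90 mm Hg, one raised filling pressure, and signs of hypoperfusion. These conditions narrow wrongful admission. They do nothing for a supported patient at or below 2.2, who has already failed the index criterion.

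**3. Order of events.**

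| Place | Order stated |
|---|---|
| Inclusion Criteria | shock first, then heart failure or infarction |
| Abstract, Methods | shock results from heart failure or infarction |
| Background and Significance | shock follows a primary cardiac pathology |

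The first row reverses the other two. It also conflicts with its own wording, because it calls heart failure and infarction etiologies, that is, causes.

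**4. Right ventricular pressure.** The criterion is printed as above 10-15 mm Hg. A value of 12 is above 10 and not above 15, so the text does not settle whether it counts. This decides eligibility only when neither the left ventricular pressure (above 18) nor the wedge pressure (above 15) qualifies the patient.

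**5. Who depends on the definition.** Number of Subjects plans approximately 200 patients before the team and 200 after. The team-era patients can be identified by activation together with documented shock. The patients from before the team cannot.

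**The case against.** The strongest reply is that these are drafting slips in a condensed article and that selection did not turn on them. The Inclusion Criteria ask for documented shock with team activation, the age and recruitment paragraphs also rest on team intervention, and the research database accepts any patient with cardiogenic shock treated at the institute. Nothing says that abstractors re-judged each chart against the index. The sequence sentence refutes itself, and the intended meaning is clear from the rest of the article. The right ventricular range is one of three alternatives.

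Much of this stands. It limits what can be said about consequences, and it makes the sequence sentence and the right ventricular range secondary to the index limb. It does not remove the contradiction. The criteria are stated wrongly, not left to a fuller document. The appeal to team activation cannot cover the controls, and the database sentence does not itself define cardiogenic shock.

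A reader might go further and infer that the wrong patients were enrolled. The documents do not show this. They do not say which rule abstractors applied, and a high index alone admits nobody, given the other required criteria.

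**Conclusion.** The point holds as a contradiction in a stated eligibility rule. Followed as printed, the index limb rejects supported patients with low output, and the sequence sentence reverses the causal order given elsewhere. The right ventricular range is a minor addition. The conclusion rests on reading the text literally and treating the listed criteria as jointly required.

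Its size cannot be determined from the documents, and two stronger inferences should be resisted.

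- **A count of affected charts.** Assuming 30% to 70% of patients on support would give 0.30 × 400 = 120 to 0.70 × 400 = 280 charts. The documents anchor no such share. The Sample Size section says 300-400 patients, not a fixed 400. The Results compare survival by use of right heart catheterization, so some patients apparently did not have it, and an index cannot be assumed for every chart. The product would also count patients on support, not patients misclassified.
- **Bias between eras.** Background and Significance lists early right heart catheterization and minimizing vasopressor and inotropic support among the team's goals, so the share on support at measurement could differ between periods. No support rate is given for either period. Neither the presence nor the direction of such bias is shown.

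The correction is still needed, because the population, and the control group in particular, cannot be reproduced from the criteria as written.

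**What to change.** - Reconcile the on-support index limb in the Inclusion Criteria with the low-output description in Background and Significance.
- Reconcile the sequence sentence with the Abstract and with Background and Significance.
- State a single right ventricular end-diastolic pressure threshold in place of the range. No cut-off is proposed here; the values are for the investigators to set.
- Apply the same corrected text to control and team-era charts.
- Confirm and record which rule the abstractors used. Re-check abstracted charts only if the printed rule was applied.

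The cost is a text correction and a check of fields already collected; no new data are needed.

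### The cardiac-index criterion for cardiogenic shock contradicts itself: without support it selects low output, with support it selects output above a cut-off

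*Protocol article*

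**What the plan says.** The criterion is in the protocol article, Methods, Inclusion Criteria. The paragraph opens "Specific criteria for the diagnosis of cardiogenic shock is defined by hemodynamic parameters" and then lists systolic pressure below 90 mm Hg, a cardiac-index condition, and a raised filling pressure (any one of three measures). It closes "and clinical signs and symptoms of hypoperfusion, such as cool extremities, decreased urine output, and altered mental status". The cardiac-index condition reads "cardiac index <1.8 L/min/m^2^ without pharmacologic support (or >2.2 L/min/m^2^ with support".

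The Introduction (Background and Significance) describes the condition three times, each time as low output:

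- Shock "is precipitated by a profound reduction in cardiac output which results in tissue hypoperfusion".
- "CS is characterized by shock occurring after a primary cardiac pathology in which cardiac output has been compromised".
- A treatment priority is "the rapid reversal of the low output state to maintain end organ perfusion".

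The Inclusion Criteria add a separate operational condition: "Enrollment criteria are specific to patients treated at the IHVI for documented cardiogenic shock with activation of the IHVI Cardiogenic Shock team". The index threshold appears nowhere else. The Participant Eligibility Criteria for the research database refer to patients with cardiogenic shock but give no hemodynamic definition.

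**The concern.** An upper limit on the index without support and a lower limit with support cannot both identify low output. As printed, the supported limb passes patients because their output is above a threshold and fails those whose output is below it.

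This matters because the paragraph is the only written hemodynamic case definition in the article, and the main comparison is survival before and after January 1, 2017. Output is also related to survival in the article's own Results. In 2017, survival was 73/78 = 93.6% among patients whose cardiac power output exceeded the 12-hour threshold, against 81/140 = 57.9% overall. Cardiac power output is a different measure from cardiac index and was taken at 12 hours, so these figures do not size the problem. They do show that an eligibility rule acting on output acts on something associated with the endpoint.

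**Working it through.** The article states no figure to reproduce here, so the check is logical.

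**Step 1. Code the rule as written.** Input: the cardiac-index condition in the Inclusion Criteria. A patient meets the output element if (index < 1.8 and no support) or (index > 2.2 and support).

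**Step 2. Evaluate it over a range of values (L/min/m²).**

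| Index | Without support | With support |
|---|---|---|
| 1.2 | meets | fails |
| 1.5 | meets | fails |
| 1.79 | meets | fails |
| 1.8 | fails | fails |
| 2.0 | fails | fails |
| 2.2 | fails | fails |
| 2.21 | fails | meets |
| 2.5 | fails | meets |
| 3.0 | fails | meets |
| 4.0 | fails | meets |

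The supported patient at 1.5 cannot be rescued by the first limb, because that limb is restricted to patients without support.

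**Step 3. Test how much hangs on the sign.** If only the supported inequality is reversed, every supported row changes from meets to fails or from fails to meets, except 2.2 exactly, which fails both versions. The unsupported column does not change. The classification of supported patients on this element therefore rests almost wholly on one character. This is a sensitivity check and does not propose a rule.

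**Step 4. Compare with the Introduction.** All three descriptions quoted above agree in direction with the unsupported column. None agrees with the supported column.

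**Step 5. Place the element among the others.** The only alternatives offered in the list are among the filling-pressure measures, so the natural reading is that blood pressure, index, filling pressure and clinical hypoperfusion are all required. On that reading:

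- a supported patient with an index of 1.5 is excluded whatever the other elements show;
- a supported patient with an index of 3.0 enters only if every other element is also met.

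The exclusion of supported low-output patients is therefore the firmer consequence.

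**The case against.** The strongest case on the other side is that the sign is a slip that never affected a record.

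- **The sign may be typographical.** It may also have arisen when the text was extracted. This is possible but cannot be shown, since the other inequalities in the sentence read sensibly. The text as it stands still needs correcting.
- **The index may not have been a strict gate.** The Results compare survival by use of right heart catheterization, so some analysed patients apparently did not have it and may have had no invasive index. Entry to the study group also depends on documented team activation. This weighs against literal use of the cut-off, but does not establish what abstractors did.
- **The index does not stand alone.** This is correct. A reader might infer that the rule admits supported patients with preserved output. With blood-pressure, filling-pressure and hypoperfusion elements listed beside it, a high index by itself does not admit anyone if all elements are required.

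A reader might also infer that the error biases the before/after comparison. The argument would be that the team lists "4) minimization of vasopressor and inotropic support" among its goals, so fewer team patients would be judged on the supported limb. The document does not support that step. The goal concerns management by the team, and no support rates at diagnosis are given for either era. Transferred patients may have had support started elsewhere. Historical controls cannot have had team activation, and no section says that they were screened with this hemodynamic list.

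Nor can a size be given. Suppose the index on support were normal with SD 0.4 and mean m. The written rule would then keep 1 − Φ((2.2 − m)/0.4) of supported patients:

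- m = 1.7: 1 − Φ(1.25) = 11%
- m = 1.9: 1 − Φ(0.75) = 23%
- m = 2.1: 1 − Φ(0.25) = 40%

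The mean, the SD and the normal shape are all assumptions, and the answer moves nearly fourfold with the mean alone. Turning this into a shift in survival would need support shares by era and a survival gradient, and the document has neither.

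**Conclusion.** The contradiction stands. The supported limb conflicts with the limb beside it and with three statements in the Introduction, and nothing in the article resolves it. Followed literally, with all listed elements required, the definition excludes supported patients with a low index, and the output element is met only by supported patients above 2.2.

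The number of patients misclassified is unknown and may be zero. Neither the presence nor the direction of a bias in the survival comparison can be established from the document. The conclusion rests only on the printed text and needs no assumption about alpha, power, effect size or sample size, none of which changes. It is an error in a decision threshold, to be corrected before the definition is relied on for analysis or reproduced elsewhere.

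**What to change.** 1. Reconcile the direction of the supported limb in the Inclusion Criteria with the unsupported limb and with the low-output descriptions in Background and Significance. The investigator should confirm the intended direction and value against the data dictionary. This review endorses neither a direction nor a cut-off.
2. State which rule the chart abstractors actually used.
3. If the written sign was applied, re-check the records classified on the supported limb with the confirmed rule, in the same way for the historical and shock-team cohorts.

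The text change is very small. If the written sign was never applied, steps 1 and 2 are the whole cost. If it was, step 3 means some repeat chart review, and more of it if no log of rejected records was kept; the article describes none.
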